## Abstract

There is a positive relationship between children’s movement competence and physical activity, with a further relationship established between physical activity and childhood obesity. The Movement Oriented Games Based Assessment (MOGBA) is a delivery and assessment intervention designed to improve children’s complex movement skills, based on principles of motor development and assessment theories. MOGBA aims to improve children’s movement competence, physical fitness and self-perceptions (physical and game) and increase children’s moderate-to-vigorous physical activity (MVPA). MOGBA is to be used in the ‘Made to Play’ initiative, involving 105 sports and activity programs across 21 countries, involving over 25 million children. A multi-site cluster randomized controlled trial will take place across three global sites (UK, Ireland and Australia). Each site will recruit eight primary schools (four experiment, four control) with each school providing two separate classes of children from age ranges 8–12 years (Site n = ~300, total n = 904). After baseline assessments, schools will be randomly allocated to an experimental or wait-list control group. Following two half-day workshops, trained facilitators will deliver the MOGBA intervention for 9 weeks. The main intervention components include delivery of 14 games-based activities with associated assessments of children’s movement and differentiation to meet children’s needs by manipulating space, effort and relationships. The primary outcome of the trial is to improve children’s’ movement competence (The Dragon Challenge), with secondary outcomes of improving children’s’ in-activity and leisure-time MVPA (5-day accelerometer), physical fitness (standing long jump and push ups) and self-perceptions (physical and game). Data will be analysed using multilevel modelling approaches. The MOGBA intervention has been designed to improve children’s movement competence and scalable interventions based on MOGBA could be applied across programs within the Made to Play initiative, globally. The trial is registered at the Australia New Zealand Clinical Trial Registry (ACTRN12619001320145p, 27 Sep 2019).

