### Sample size calculation

A sample size calculation was completed to estimate the number of schools needed for the trial. Sampling for a two-group clustered RCT is developed around data from previous clustered trials assessing game skill (e.g., support, decision-making and defence) and fundamental movement skill (e.g., throw, kick, under-arm throw and catch) development [23, 24]. The lowest effects in these trails were observed for the fundamental movement skill of catch (effect *d* = 0.4), and the game skill of decision making (*d* = 0.4).

Without accounting for clustering among schools (schools being alike and reducing the power of data), approximately 156 students are required to detect an effect of d = 0.4 at 80% power with alpha 0.05. To adjust for clustering, the following correction factor is applied (1+ (m– 1) x ICC) [25], where m = students per school and ICC = the intra-class correlation coefficient (between school variance / between school variance + within school variance). Assumptions are based on clustering at the school level (one class recruited per school, with ~25 students per class), and a conservative ICC of 0.20 based on data from a school based intervention [22], resulting in a correction factor of 5.8. The resulting student sample is ~904 students at 36 schools (18 intervention, 18 control).

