### Setting and participants

To align with the typical motor development phase associated with CMS, recruitment of participants will be targeted at children 8–12 years, spread across 4 school years/grades. As this age range straddles two levels of schooling (primary/elementary, secondary/middle) 6 schools from each level at each site will be invited to the trial. Existing university networks will be used to recruit schools and if more than the required number of schools replies positively, schools will be stratified into age groupings prior to random selection (coin toss) of inclusion into the study. Recruitment will result in 3 sites each containing 12 schools (6 experiment, 6 control) evenly distributed across primary/elementary, secondary/middle schools yielding approximately 300 students at each site and a total of ~904 students for the trial. Representatives of each school will be invited to an information event to support their decision-making in becoming involved.

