### Coach workshops

Two, three hour, workshops involving a mixture of theory and practical content, designed by the Principle Investigator and lead investigator from each of the sites (site lead) will be delivered by each site lead, in- country, to four facilitators. The format of the coach learning session will be: (i) the nature of children’s movement development, (ii) rationale, structure and purpose of MOGBA, (iii) intervention programme of activities, (iv) changing the challenge, (v) differentiating opportunities (vi) assessing and recording movement competence and (vii) using assessment to guide teaching and improve movement competence.

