### Statistical analyses

This trial aims to examine whether MOGBA (a) improves children’s movement competence (Dragon Challenge); (b) increases MVPA during PE lessons (acceleromters), (c) reduces sedentary time both in school and outside of school (accelerometers) (d), improves physical fitness (plank and standing long jump), (e) improves self-perceptions of game and physical competence (Game Play Perception Profile). We hypothesize that children in the MOGBA intervention, compared to those in the control group, will display more favorable changes in these variables identified above.

Statistical analyses of the primary and secondary outcomes will be conducted with linear mixed models using IBM PASW Statistics 25 (SPSS Inc. Chicago, IL) software. Impacts are estimated using an intention-to-treat (ITT) approach, with alpha levels set at p < 0.05. Linear mixed models will be fitted to compare continuous outcomes. Group, time, and group-by-time interaction will be assessed as fixed effects within the model, with covariates of gender and year level also included as fixed effects. The school a student belongs to and the research site will be included as a random intercepts within the model to account for the multi-level nature of the data, and subject (student ID) will be included as a random intercept to model repeated measures at the individual level. Differences of means and 95% confidence intervals (CIs) will be determined using the linear mixed models. If the variables used for secondary outcomes (questionnaires) fail tests of multivariate normality, non-parametric methods will be utilised, or the variables for use in the linear models will be an individual’s factor score from a confirmatory factor analysis of the scales with the appropriate estimator chosen given the non/normal nature of the data.

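### The abstract's 24 primary schools with two classes each contradict the 36 primary and secondary schools with one class each used elsewhere, and the shared total of about 904 children fits only the 36-school design

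*Protocol article*

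**What the plan says.** The Abstract describes the recruitment as follows: "Each site will recruit eight primary schools (four experiment, four control) with each school providing two separate classes of children". It gives about 300 children per site, 904 in total, and three sites.

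The methods describe something else:

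- Setting and participants: "Recruitment will result in 3 sites each containing 12 schools (6 experiment, 6 control) evenly distributed across primary/elementary, secondary/middle schools", again with about 300 children per site and about 904 overall.
- Sample size calculation: the clustering assumption is "one class recruited per school, with ~25 students per class", and the result is about 904 students at 36 schools, 18 per arm.
- Randomization: schools are ranked and paired within primary/elementary and secondary/middle strata.

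The power inputs, all from Sample size calculation, are "approximately 156 students are required to detect an effect of d = 0.4 at 80% power with alpha 0.05" and "a conservative ICC of 0.20 based on data from a school based intervention". The ICC is defined there at school level, as "between school variance / between school variance + within school variance". Statistical analyses gives the test level only as "with alpha levels set at p < 0.05". Neither section says whether the test is one-sided or two-sided.

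**The concern.** The two descriptions differ on number of schools (24 or 36), classes per school (two or one) and school level (primary only, or primary and secondary). Both are current text. The only deviation that the article declares, in Trial design, is the drop from four sites to three. The abstract already has three sites, so that change does not explain the difference.

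In a trial randomised by school, the number of schools and the children per school largely determine power. Carrying the same 904 under both structures suggests that they are interchangeable, and they are not. School level also decides which children the result applies to, and whether the strata used for randomisation exist at all: a primary-only trial has no secondary stratum.

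**Working it through.** **Inputs.** d = 0.4, alpha 0.05, power 80%, unclustered total 156, ICC 0.20, and design effect 1 + (m − 1) × ICC with m = students per school (all from Sample size calculation). School numbers come from the Abstract and from Setting and participants.

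**Step 1: reproduce the plan's figure.** The number per arm is 2(z_α + z_β)²/d².

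- One-sided alpha 0.05: 2 × (1.645 + 0.842)²/0.16 ≈ 77.3, rounded up to 78 per arm, 156 in total. This matches the plan.
- Two-sided alpha 0.05: 2 × (1.960 + 0.842)²/0.16 ≈ 98.1, rounded up to 99 per arm, 198 in total. This does not match.
- Design effect at m = 25: 1 + 24 × 0.20 = 5.8.
- 156 × 5.8 = 904.8, and 904.8/25 = 36.2 schools. 36 × 25 = 900, consistent with about 300 per site.

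So 904 is the product of one class of 25 per school, and it belongs to the 36-school version.

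**Step 2: apply the same method to 24 schools.** Effective n = K·m/[1 + (m − 1) × 0.20], with K the number of schools. Power ≈ Φ(0.4 × √(effective n/4) − z_α).

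| Schools | Children per school | Design effect | Effective n | Power, one-sided | Power, two-sided |
|---|---|---|---|---|---|
| 36 | 25 | 5.8 | 155.2 | 80.1% | 70.2% |
| 24 | 904/24 = 37.7 | 8.33 | 108.5 | 66.9% | 54.9% |
| 24 | 50 | 10.8 | 111.1 | 67.8% | 55.9% |
| 24 | no limit | – | 24/0.20 = 120 | 70.7% | 59.1% |

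Example for 904 children in 24 schools: 0.4 × √(108.5/4) = 2.083. One-sided, Φ(2.083 − 1.645) = 66.9%. Two-sided, Φ(2.083 − 1.960) = 54.9%.

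With a t distribution on K − 2 degrees of freedom instead of the normal, the one-sided figures are 78.7% (36 schools of 25) and 64.6% (24 schools, 904 children). The two-sided figures are 67.7% and 51.3%. The size of the loss is similar.

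**Step 3: how far this depends on the ICC.** With 904 children in 24 schools, effective n reaches 156 when ICC = (904/156 − 1)/(37.67 − 1) = 0.131. It reaches the two-sided requirement of 198 when ICC = (904/198 − 1)/36.67 = 0.097.

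**The case against.** The strongest reply is that this is one unsynchronised sentence and not a rival design. The Sample size calculation and Setting and participants sections agree on 36 schools, and Randomization uses the same two school levels. The arithmetic leads to 36 schools. The abstract also departs from the body elsewhere: it lists push ups where the methods use a plank, and leisure-time activity where the methods measure activity in school. That stands, and it makes correcting the abstract the likely remedy. It does not remove the contradiction in three features that determine power and the target population.

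A second reply concerns the ICC. The plan calls 0.20 conservative and sets it with one class per school, where class and school variation cannot be separated. With two classes per school, part of that correlation might not be shared across classes. As an assumption, hold the within-class correlation at 0.20 and let children in different classes of the same school correlate at 0.10 or 0.05. With 904/48 = 18.8 children per class, the design effect is 1 + 17.8 × 0.20 + 18.8 × 0.10 or 0.05. Power is then about 77% or 82% one-sided (66% or 73% two-sided). This stands as a limit on the power result. The plan itself, however, defines its ICC as between-school variance and claims no such gain.

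A reader might infer four stronger things that the documents do not support:

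- *That training four facilitators per site confirms four intervention schools.* Coach workshops says the training "will be delivered by each site lead, in- country, to four facilitators", but nothing requires one facilitator per school or prevents one from covering two. The count fits either version.
- *That the abstract contradicts itself because 24 × 2 × 25 = 1200.* The abstract gives no class size. The conflict arises only if the methods' figure of about 25 is carried over; otherwise 904/48 is about 19 per class.
- *That 24 schools can never reach the stated power.* The ceiling of 120 holds at a between-school ICC of 0.20, not in general.
- *That power falls from 80% to about 55%.* That sets a one-sided starting point against a two-sided result.

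**Conclusion.** The contradiction is established from current text, and 904 is justified only for 36 schools of about 25. If the abstract's 24 schools were used with 904 children, effective n would be about 108, and at most 120 however many children were tested, against 156 required. Like for like, power at d = 0.4 drops from 80% to about 67% one-sided, or from about 70% to about 55% two-sided.

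These figures rest on the plan's between-school ICC of 0.20, its own design effect formula, equal school sizes and the normal approximation. They take no credit for baseline adjustment or pairing, which the calculation does not claim either. A school-level ICC of about 0.13 or lower would restore 80% one-sided (about 0.10 or lower two-sided). That 156 reproduces only one-sided, leaving 36 schools at about 70% two-sided, is a separate matter and is not charged to the school count here.

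The point needs correcting before the stated sample size can be relied on.

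**What to change.** State one design throughout.

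- **If 36 schools is the real design**, which the methods sections support, change the abstract to 12 schools per site (six per arm), primary/elementary and secondary/middle, one class of about 25 per school. This costs only a text edit.
- **If 24 primary schools with two classes each will run**, recompute the design effect with the actual number of children per school and restate the power: about 67% one-sided or 55% two-sided at ICC 0.20 with 904 children. Remove the schooling-level split from Setting and participants and the strata from Randomization. The cost is a less favourable stated power. If a lower between-school ICC is used instead, it should be justified in the text. Keeping ICC 0.20 and the one-sided 80% would need more than 156 × 0.20 = 31.2 schools, whatever the class size.

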## Introduction

The ability to perform various movement skills (e.g. running, kicking, jumping, throwing) in a skilful manner is often defined as movement competence [1, 2]. Goodway, et al. [1] state that these skills can be separated into three discrete constructs: locomotor (run, hop, jump, slide, gallop, leap); object control (strike, dribble, kick, throw, underarm roll, catch); and stability skills (non-locomotor skills such as body rolling, bending, and twisting). Collectively, these are known as Fundamental Movement Skills (FMS) and are considered to be the foundation skills that enable the specialised sequences of movement required for participation in many organised and non-organised physical activities for children and adolescents [1, 3]. Furthermore, a positive relationship has been established between children’s participation in physical activity (PA) and movement competence [4–7] and PA has been recognized as supporting broader constructs of children’s development within the cognitive, psychological and emotional domains [8, 9].

A key developmental stage within a child’s movement development is the transition from FMS to what we are defining as Complex Movement Skills (CMS) [1, 10]. CMS are mature movements that have been refined and combined in increasingly complex environments that can be used in a range of sports and physical activity movement settings, as children socially orientate to these environments. Within the CMS development phase, improvements are seen in the way in which the child performs the movement skill or pattern with greater accuracy, co-ordination and control [1]. The rate that children acquire and become competent in performing FMS is influenced by physical attributes (e.g. height, genetics, maturity) and environmental conditions created by teachers and coaches, such as opportunities for practise, instruction, encouragement and feedback [11].

There is a raft of FMS assessment frameworks that have been validated, refined and used cross-sectionally to understand the movement competence of children [12]. Typically, movement assessments have been designed to assess children at the FMS stage of development and are intended for use by clinicians and researchers, deeming them unsuitable for use by teachers in a practical environment [13, 14]. It has been suggested that involving practitioners responsible for delivering children’s sport and PA classes in the assessment of children’s movement skills would enable practitioners to better support children’s development of FMS [15]. In recent years, a selection of FMS assessment tools has been developed with teachers and practitioners in mind as the assessor (e.g. Canadian Assessment Movement Skill and Agility [CAMSA] [16]; Dragon Challenge [17]). CAMSA has been designed and validated to assess children aged 8–14 years old and requires children to complete a movement-based course including seven skills that reflect *real world* abilities [18, 19]. Dragon Challenge is similarly dynamic in nature in that participants are assessed over a timed obstacle course, rather than being assessed one skill at a time in isolation as seen in all other FMS assessments.

Whilst these measures move towards the assessment of a child’s movement competence in a more dynamically framed and, therefore, ecologically appropriate environment, there is still a lack of interaction with other children as they would typically experience within games [20]. To address this shortfall, a Movement Oriented Games Based Assessment (MOGBA) has been designed to provide an appropriate range of games-based activities and associated assessment framework to develop and assess children’s CMS competence within a dynamic and fluid environment. The aim of this paper is to outline the rationale and study protocol for a MOGBA cluster randomized controlled trial.

### The Made to Play (MTP) context

The MTP initiative aims to support 105 programs across 21 countries in providing ‘opportunities to get children moving so that they can lead happier, healthier and more successful lives’ [21]. To achieve this, one of their objectives is to support coaches within MTP programs to develop the movement competence of children aged 8–12 years by providing a delivery and assessment framework. The programs supported by MTP are wide-ranging, containing the full spectrum of individual (e.g. running, skateboarding) and team (e.g. basketball, soccer) sports. MTP programs are delivered in a range of settings (e.g. schools, recreational centres, sports clubs) using varying models and patterns of delivery in both participation and performance domains, with group sizes typically between 15 and 30 children.

## Materials and methods

### Ethics

Sheffield Hallam University Ethics Committee granted ethical approval (ER18592084), with extension to 2022. The University of Newcastle, Australia, has also granted ethics approval (H-2020-0066). The trial is registered at the Australia New Zealand Clinical Trial Registry (ACTRN12619001320145p, 27 Sep 2019). Written consent will be obtained from participants.

### Trial design

A cluster randomized control trial will be used to assess the effectiveness of MOGBA in a school setting, as this is perceived to be an ideal setting for the promotion of movement competence and PA [22]. Another potential option available was to establish the trial within MTP programs, as clusters. It was felt that, due to the eclectic and disparate nature of these programs, controlling and accounting for the variability both within intervention and control groups would be more problematic than a school setting. It is intended to use the findings of this trial to inform the scalability of MOGBA across MTP programs.

Through the trial we aim to examine whether MOGBA (a) improves children’s movement competence; (b) increases Moderate to Vigorous Physical Activity (MVPA during PE lessons, (c) increases MVPA time in school (d), improves physical fitness, (e) improves self-perceptions of game and physical competence. We hypothesize that children in the MOGBA intervention, compared to those in the control group, will display more favorable changes in movement competence, physical activity, physical fitness, physical self-perceptions and game perceptions.

The 9-week intervention will be delivered during the school day and target children in the school years containing the age ranges 8/9, 9/10, 10/11, 11/12 years. Baseline measures, including all primary and secondary outcomes, will be taken prior to the commencement of the intervention, which will be staggered across the sites to prevent clashes with key educational milestones within the respective countries. This is a deviation from the original study protocol in which there was originally 4 sites, including the USA, which was subsequently reduced to 3 sites as a result of Covid-19 restrictions on accessing schools. After baseline measures are taken, schools will be randomly allocated into either an intervention or wait-list control group. Schools allocated to the experimental group will be assigned a facilitator to deliver the 14 MOGBA activities across a 9-week period.

By contrast, the wait-list control group undertakes the standard content planned by their teachers across the intervention period. This content will vary from country to country and will also be subject to change based on the seasonality of delivery across the RCT. As each site has its own control group, it is not expected that heterogeneity among the countries will introduce bias. Additionally, as the countries involved have relatively similar physical education programs expressed through the development of movement skills with transference into game and sport based activities, the differences related to individual sites is likely minimal. All countries will follow some sort of Physical Education curriculum, whether that is determined at national, provincial or regional level. All primary and secondary outcomes will be assessed at 3-month post-test with the exception of in-school physical activity, which will be assessed between weeks 7–9 of the intervention period to assess the impact of the program on student in-school MVPA. Schools from the wait-list control group will receive the MOGBA program after the completion of post-test assessments.

### Sample size calculation

A sample size calculation was completed to estimate the number of schools needed for the trial. Sampling for a two-group clustered RCT is developed around data from previous clustered trials assessing game skill (e.g., support, decision-making and defence) and fundamental movement skill (e.g., throw, kick, under-arm throw and catch) development [23, 24]. The lowest effects in these trails were observed for the fundamental movement skill of catch (effect *d* = 0.4), and the game skill of decision making (*d* = 0.4).

Without accounting for clustering among schools (schools being alike and reducing the power of data), approximately 156 students are required to detect an effect of d = 0.4 at 80% power with alpha 0.05. To adjust for clustering, the following correction factor is applied (1+ (m– 1) x ICC) [25], where m = students per school and ICC = the intra-class correlation coefficient (between school variance / between school variance + within school variance). Assumptions are based on clustering at the school level (one class recruited per school, with ~25 students per class), and a conservative ICC of 0.20 based on data from a school based intervention [22], resulting in a correction factor of 5.8. The resulting student sample is ~904 students at 36 schools (18 intervention, 18 control).

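### The starting figure of 156 students is a one-sided 5% calculation; redone two-sided on the plan's own inputs, 36 schools give about 68–70% power for d = 0.4, not 80%

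*Protocol article*

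**What the plan says.** The *Sample size calculation* section of the protocol article takes d = 0.4, the lowest effect in the earlier trials it draws on, and says that "approximately 156 students are required to detect an effect of d = 0.4 at 80% power with alpha 0.05". It does not say whether alpha is one-sided or two-sided. It then inflates for clustering, assuming "one class recruited per school, with ~25 students per class" and an ICC of 0.20, which gives a factor of 5.8, and concludes: "The resulting student sample is ~904 students at 36 schools (18 intervention, 18 control". *Setting and participants* repeats this design as 12 schools at each of 3 sites.

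The *Statistical analyses* section plans linear mixed models "with alpha levels set at p < 0.05" and adds: "Differences of means and 95% confidence intervals (CIs) will be determined using the linear mixed models". The hypothesis is directional, in that intervention children "will display more favorable changes in these variables identified above". No section mentions a one-sided test or a 90% interval.

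**The concern.** The sample size paragraph and the analysis paragraph appear to use different error rates. A 95% confidence interval corresponds to a two-sided 5% test, and a two-sided 5% test for d = 0.4 with 80% power needs roughly 200 students before clustering, not 156. The gap is multiplied by 5.8 and carried into the number of students and schools.

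At stake is the article's only power statement. The effect of 0.4 was chosen as the smallest seen in the earlier trials, so a design that reaches 80% power only at a larger effect misses the target it set. A null primary result would also be read as firmer evidence of no effect than the design supports, in a trial meant to inform wider use of the programme.

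**Working it through.** **Inputs.** From *Sample size calculation*: d = 0.4 (SD = 1), power 80%, alpha 0.05 with sidedness not stated, m = 25 per school, ICC = 0.20, 36 schools, 18 per arm. From *Statistical analyses*: a 0.05 threshold and 95% confidence intervals.

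**1. Reproduce the plan's figure.** Normal approximation: n per arm = 2 × [(z for alpha + z for power) / d]².

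| | z for alpha | n per arm (normal) | n per arm (t-test) | Total |
|---|---|---|---|---|
| One-sided 5% | 1.645 | 2 × [(1.645 + 0.842)/0.4]² = 77.3 → 78 | 77.97 → 78 | 156 |
| Two-sided 5% | 1.960 | 2 × [(1.960 + 0.842)/0.4]² = 98.1 → 99 | 99.08 → 100 | 198 to 200 |

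The design effect is 1 + (25 − 1) × 0.20 = 5.8. Then 156 × 5.8 = 904.8, and 904.8 / 25 = 36.2 schools. The whole published chain is reproduced, but only from the one-sided row.

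**2. Other routes to 156.** A two-sided calculation also gives 156 at 70% power for d = 0.4, or at 80% power for d = 0.45. Neither is what the article states. A two-sided analysis of covariance with a baseline correlation of about 0.45 to 0.46 would come to about 156, but the section mentions no correlation.

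**3. Two-sided power of the stated design.** No credit is taken for baseline or covariates.
- Effective n = 36 × 25 / 5.8 = 900 / 5.8 = 155.2.
- Standard error of the standardised difference = 2 / √155.2 = 0.1606.
- Non-centrality = 0.4 / 0.1606 = 2.49.
- Normal: Φ(2.49 − 1.96) = 70.2%.
- t with 36 − 2 = 34 df: 67.7%.

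Using 904 students instead of 900 gives 70.4% and 67.9%.

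**4. Effect detectable with 80% power.** Normal: (1.960 + 0.842) × 0.1606 = 0.450. With t on 34 df: 0.463.

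**5. Size needed for 80% at d = 0.4, two-sided, same method.** 198 × 5.8 = 1,148 and 200 × 5.8 = 1,160 students. In schools of 25, that is 46 schools by the normal approximation (80.4%) or 48 with a school-level t (80.4%).

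**6. What a baseline correlation r of school means would do.** This assumes equal variance at both times.
- Group-by-time contrast (difference in change): the variance is multiplied by 2(1 − r). At r = 0.5 the factor is 1.0, so power stays at 67.7%. At r = 0.62 it is 79.3%, and at r = 0.63 it is 80.3% (t, 34 df).
- Baseline as a covariate: the factor is 1 − r². At r = 0.5 it is 0.75 and power is 79.7% (t, 33 df).

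**7. Dependence on the number of schools.** The *Abstract* gives eight schools per site, so 24 in all. With about 904 students, m = 904 / 24 = 37.7, the design effect is 1 + 36.7 × 0.20 = 8.33, and effective n is 108.5. Two-sided power is then about 51% (t, 22 df).

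**The case against.** *The test may be meant as one-sided.* The sample size section says only alpha 0.05, and the hypothesis is directional. That 156 is one-sided is an inference from the numerical match. But a directional hypothesis does not declare a one-sided test, and the 95% intervals point the other way. If one-sided testing was intended, the article has to say so, so the text needs correction on either reading.

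*The planned analysis is not the one computed here.* This stands. A reader might infer that the trial as planned has 68–70% power. The documents do not support that. The analysis section plans a repeated-measures model with baseline data, gender and year level, and *Randomization* pairs schools on socio-economic rank within school level. None of this enters the 68–70%, and actual power could be higher or lower.

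*Baseline data would restore 80% anyway.* A reader might infer that a correlation of 0.5 is enough. That holds only with baseline as a covariate. The analysis section specifies group, time and their interaction, and for that contrast a correlation of 0.5 gains nothing.

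*The ICC is described as conservative.* With an assumed ICC of 0.15, two-sided power would be about 78%; with 0.12, about 84% (t, 34 df). This bears on the practical consequence, but it does not make 156 the right answer to the stated inputs.

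*Null results can be read from the interval.* True, and neither type I error nor the estimates are affected. The error is confined to the power statement.

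**Conclusion.** Wrong as written. On the stated inputs, 156 students, and so about 904 students in 36 schools, follow only from a one-sided 5% test that the article does not declare and that its 95% intervals contradict. Corrected to two-sided, the published calculation gives about 68% to 70% power for d = 0.4, an overstatement of 10 to 12 percentage points. Put the other way, 80% power is reached at d of about 0.45 to 0.46.

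This rests on 36 schools of 25, ICC 0.20, no loss to follow-up (the calculation includes no allowance for it) and no credit for baseline. It applies to the 36-school design in *Sample size calculation* and *Setting and participants*. If the abstract's 24 schools were the real design, power by the same method would be lower, about 51%.

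A reader might also infer from the two-sided requirement that the trial must recruit 46 to 48 schools. That does not follow: it would be needed only to claim 80% at d = 0.4 without using baseline data.

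**What to change.** In *Sample size calculation*, state that alpha is 0.05 two-sided. Replace the 80% claim with: 36 schools of about 25 students, ICC 0.20, give about 68–70% power for d = 0.4, or 80% power for d of about 0.45 to 0.46, without credit for baseline.

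If 80% at d = 0.4 is still to be claimed with 36 schools, state the assumed baseline to post-test correlation of school means, give its source, and match it to the model: about 0.63 for the planned group-by-time contrast, or about 0.5 only if the analysis section is changed to enter baseline as a covariate. If a one-sided test was intended, declare it in both sections and bring the intervals into line with it.

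Confirm the number of schools when restating the figure, because the power depends on it.

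The cost is a rewritten paragraph and a less favourable power figure. No extra schools are needed to make the statement correct.
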